**Figure 2. f2:**
[figure not shown]
Figure depicting the timelie of the experimental procedure.

**
*VR spatial task condition*
**

 Training: The participants will be placed in our virtual environment and instructed to explore the space around them in each of the scenes. In each scene, the participant will see 3 objects at a time (two in front of him and one behind him).

Testing: After the training is completed, participants will be asked to start the testing phase. This phase will last until the task is completed, namely, when the participant accurately recalls the position of the objects after three consecutive correct trials. The objects are those learned during the training phase. The participants' accuracy and reaction time will be recorded.

**
*AV memory task condition*
**

Administration of the RAVLT will involve several steps:

The experimenter will read the first list (List A) of 15 unrelated words at a rate of about one word per second. It's crucial to present the words in the same order and with the same pronunciation for each participant. After presenting the list, the participant will be asked to repeat back as many words as they can remember, regardless of the order. After the participant recalled as many words as possible from List A, the process will be repeated for five immediate recall trials. After each trial, the number of words correctly recalled will be recorded. 

The experimenter will read a second list (List A) of 15 unrelated words (List B) to the participant and instruct them to recall as many words as possible from this list. This step is designed to interfere with the participant's ability to recall words from List A. Following the presentation of List B, the participant will be asked to recall the words from List A once again. This step assesses the individual's ability to retrieve information from memory after interference.

After a short delay in which the participant will have to do a scrambled image test (usually around 20–30 minutes), the participant will be asked to recall the words from List A once more without presenting the word list again. This step evaluates the individual's ability to retain information in memory over time.

The participant's performance will be scored based on the number of words correctly recalled or recognized during each test phase.

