We will use a series of tests and tasks to validate the VSCT. We hypothesize a positive correlation between the VSCT and SCT, as both are designed to measure the same construct—namely, the ability to form cognitive maps. We also hypothesize a positive correlation between the VSCT and Backward Corsi, as working memory is a key component in the formation and maintenance of cognitive maps (
Epstein *et al.*, 2017). Conversely, we do not expect a significant correlation between the VSCT and RAVLT. We included the Rey Auditory Verbal Learning Test (RAVLT) in our study precisely to assess discriminant validity. The RAVLT measures verbal episodic memory, while the VSCT targets visuospatial configuration memory—two constructs that are theoretically and empirically distinct (
Suri *et al.*, 2017). By including the RAVLT and confirming that it does not significantly correlate with performance on the VSCT, we provide evidence that the VSCT is not simply capturing general memory ability, but rather a more specific visuospatial memory component. This lack of correlation supports the discriminant validity of our task, helping to confirm that it measures a construct different from that assessed by standard verbal memory tasks.

Finally, to evaluate VSCT feasibility we will use the Simulator Sickness Questionnaire (SSQ) (
Kennedy *et al*., 1993).

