**Figure 1. f1:**
[figure not shown]
**a.** Main menu interface presented at the beginning of each scene, allowing participants to change scenes, return to the home screen, or exit the task.
**b.** Example view of the full environment, showing all five objects placed in a triangular configuration. This layout illustrates the type of spatial arrangement participants are required to learn.
**c.** At the start of each trial, only the two front objects are visible to the participant, who must respond to a question about the missing (third) object based on memory. A floor circle indicates the location of the hidden object.
**d.** If the participant selects the wrong answer, the environment allows them to rotate and discover the third object's location. This feedback mechanism supports gradual learning of the spatial configuration.

The location of the missing object was indicated by a circle on the floor (
Figure 1c/d), providing a visual landmark to aid participants. An interactive interface allowed participants to switch scenes by pressing "change", return to the main menu with "VSCT", and exit by pressing "exit" (
Figure 1a). Participants could explore objects around them for a maximum of 20 seconds per scene.

From the beginning of the task, participants were prompted with questions about the spatial location of objects. Each scene included a canvas displaying a question (e.g., "Which object is behind you?") with three possible choices representing the missing object. Only the two adjacent objects in front of the participant were shown (
Figure 1b). Button positions were randomized to avoid spatial response biases. Participants learned the correct answers through trial and error, gradually forming internal representations of the spatial configurations based on feedback. The task consisted of 40 such trials. For each trial, the participant’s response was recorded.

**
*Environment exploration*
**

Participants could rotate and inspect the environment by moving right or left, using the Unity Interaction Toolkit and custom scripts to interface with the HMD joysticks. Users’ movements are continuous and based on the participant's head direction to ensure ecological validity with proprioceptive feedback and reduce motion sickness.

**
*Data repository*
**

At the end of the project, the project source code will be published in a dedicated public repository on Git Hub to encourage further development and research (
https://github.com/[name]/VSCT). 

**

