### Correlation analysis

We will run correlations matrix between CORSI, SBSOD, and hits at both the VSCT and SCT. This will help us understand the influence of general intelligence and working memory capacity on spatial ability and ensure that the VSCT and SCT are comparable tasks

Regarding reliability, we plan to assess internal consistency using split-half and/or Cronbach’s alpha methods for key performance metrics (e.g., accuracy, error scores), depending on distributional characteristics. In addition, we aim to conduct a test–retest reliability study in a subsample of participants to examine stability over time.

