### Expected results

**
*Validation of VSCT outcomes*
**

We expect SCT mean accuracy to be positively correlated with performance on the CORSI backward task and VSCT accuracy.

A positive correlation with SCT accuracy would validate VSCT as a measure of participants' abilities to maintain and retrieve cognitive maps based on allocentric frameworks (
Burles *et al*., 2017). Both SCT and VSCT require creating an allocentric cognitive map from multiple egocentric viewpoints. Therefore, we expect a positive correlation between SCT mean accuracy and spatial working memory, as measured by the Corsi backward task. Regarding reliability, based on our planned analyses, we expect to find acceptable to high internal consistency for key performance metrics (e.g., accuracy, error scores), as assessed through split-half reliability and/or Cronbach’s alpha, depending on the distributional properties of the data. Additionally, we anticipate that test–retest reliability in a subsample will demonstrate moderate to high stability over time, supporting the robustness of both the SCT and VSCT as reliable tools for assessing spatial cognition.

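### The VSCT is given two incompatible lengths and two scores; if three correct in a row ends the whole test and raw hits are scored, the hypothesised positive correlation with the SCT would turn negative

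*Protocol article*

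**What the plan says.** Under The virtual task, the protocol article describes a question "with three possible choices representing the missing object" and says: "The task consisted of 40 such trials". Under VR spatial task condition, the testing phase is instead open-ended. It lasts until completion, which is defined as "namely, when the participant accurately recalls the position of the objects after three consecutive correct trials". No maximum is given. Nothing says that 40 is a cap, that the 40 trials belong to training, or that the criterion applies scene by scene.

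The score also varies. Under VR spatial task condition, "accuracy and reaction time will be recorded". Under Correlation analysis: "We will run correlations matrix between CORSI, SBSOD, and hits at both the VSCT and SCT". Under Expected results: "We expect SCT mean accuracy to be positively correlated with performance on the CORSI backward task and VSCT accuracy".

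The direction of the validating result is fixed in the introduction (Validation of a new 3D spatial task): "We hypothesize a positive correlation between the VSCT and SCT". The comparator, the SCT, has a fixed 40 items (Procedure). Correlation analysis also plans split-half reliability and/or Cronbach's alpha.

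**The concern.** A count of correct answers measures ability only if everyone answers the same number of questions. If a run of three correct answers ends the test, a perfect participant stops with 3 hits, the lowest score anyone who meets the criterion can have. Weaker participants stay longer and collect more. The count then runs against ability, while the validity hypothesis needs a positive correlation.

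Proportion correct avoids the reversal but rests on very few trials for many participants. Because the text fixes neither the length nor the score, the SCT-VSCT correlation that is meant to validate the task could be positive, weakened or negative for the same participants, depending on which sentences are followed.

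**Working it through.** There is no derived figure in the article to reproduce here. The 40 trials and the run of three are design constants.

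**Inputs from the article.** Fixed length of 40 trials; stop at 3 consecutive correct; chance level 1/3 (three options); SCT of 40 items.

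**Assumption.** The article gives no per-trial probability of a correct answer, p. The range from chance (1/3) to 1 is shown.

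**Expected hits.**
- Fixed length: E[hits] = 40p.
- One stop at three in a row, no cap: E[trials] = (1 - p³) / ((1 - p)p³), and E[hits] = p × E[trials].
- The same stop with a 40-trial cap: exact recursion on the current run length.

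Worked values without a cap:
- p = 1/3: (26/27) / ((2/3)(1/27)) = 39 trials; 39/3 = 13 hits.
- p = 0.6: 0.784 / (0.4 × 0.216) = 9.07 trials; × 0.6 = 5.44 hits.
- p = 0.9: 0.271 / (0.1 × 0.729) = 3.72 trials; × 0.9 = 3.35 hits.

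| p | Hits, 40 fixed trials | Hits, run of three, no cap | Hits, run of three, cap 40 |
|---|---|---|---|
| 1/3 | 13.3 | 13.0 | 8.6 |
| 0.5 | 20 | 7.0 | 6.8 |
| 0.6 | 24 | 5.4 | 5.4 |
| 0.7 | 28 | 4.5 | 4.5 |
| 0.9 | 36 | 3.35 | 3.35 |
| 1.0 | 40 | 3.0 | 3.0 |

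From chance upward, the count rises with ability under the fixed length and falls under the run rule, with or without a cap. The criterion also separates poorly at the bottom: a pure guesser meets it within 40 trials with probability 0.647.

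**Correlation with a 40-item SCT, by simulation.** Assumptions: latent correlation 0.6 to 0.8, mean accuracy 0.64, SD 0.12 to 0.16, one stop for the whole test, cap of 40 trials.

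| VSCT rule and score | Correlation with SCT |
|---|---|
| 40 fixed trials, hits or proportion correct | +0.43 to +0.65 |
| Run of three, raw hits | -0.19 to -0.33 |
| Run of three, proportion correct | +0.26 to +0.45 |
| Run of three, reversed trials-to-criterion | +0.24 to +0.40 |

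Median test length under the run rule was 6 trials, and 29% to 31% of simulated participants stopped at exactly 3.

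**Sensitivity.** With other ability ranges (p from 1/3 to 1, 0.4 to 0.95, or 0.5 to 0.95) and latent correlations of 0.5 to 1.0, the raw-hits correlation stayed negative, from about -0.17 to -0.50. With p rising through learning, at latent correlation 0.7, it was about -0.27 for raw hits and +0.22 for proportion correct.

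**Reliability.** Cronbach's alpha needs the same items for everyone. Under the run rule, lengths start at 3 trials and differ between people, and every record that meets the criterion ends in three correct answers by construction.

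**The case against.** A reader might infer that the study would necessarily give the wrong answer about the VSCT. The article does not support that, for two reasons.

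First, the hit count is not the only score named. The procedure and the expected results speak of accuracy. If that means proportion correct, the sign is preserved. Assuming the stated 166 participants split equally, 83 would take the VSCT. The power of a two-sided 5% test is then about Φ(atanh(r) × √80 - 1.96): 0.66 at r = 0.26 and 0.99 at r = 0.45. That is a loss of precision and an understated correlation, not a reversed conclusion.

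Second, the criterion might be meant per scene. There are 5 testing scenes and 5 × 8 = 40. Under the same assumptions, a per-scene stop capped at 8 trials gives +0.11 to +0.19 for raw hits and +0.41 to +0.63 for proportion correct, so nothing reverses and accuracy loses little. The article states no such rule or cap, however. With a loose cap of 40 trials per scene, raw hits go negative again (-0.35 to -0.54).

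It would also be too strong to say that split-half reliability cannot be computed. Halves of a proportion can be formed, but they are imprecise with so few trials. The objection to alpha stands.

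What remains is that two stated lengths and two stated scores are unreconciled, and one combination of them reverses the key correlation.

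**Conclusion.** The contradiction is in the text and needs no assumption. The article defines the length of the instrument it validates in two incompatible ways and names its score in two ways.

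The reversal is conditional on a raw hit count with a single stop for the whole test. In that case the direction holds over the whole range from chance to perfect accuracy. Its size, about -0.2 to -0.3, rests on the assumed ability distribution and latent correlation. With proportion correct the effect is attenuation only. Either way, the validity correlation cannot be interpreted until one length and one score are fixed, so this should be settled before data collection.

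**What to change.** Reconcile The virtual task with VR spatial task condition. Give every participant the same 40 test trials and score the VSCT as number correct out of 40, which is equivalent to proportion correct and matches the 40-item SCT. Use that one score in VR spatial task condition, Correlation analysis and Expected results. If a three-in-a-row criterion is kept, state that it applies to training only.

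The cost is a change of wording and of the task software, and somewhat longer testing for fast learners; the article does not give the time per trial. A ceiling effect is possible because feedback teaches the answers. The simulations of 40 fixed trials held each person's accuracy constant and did not test this.

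If the criterion must end testing, do not use raw hits, do not compute alpha, and state that the correlation will be attenuated. Re-scoring as reversed trials-to-criterion is not a cure: at +0.24 to +0.40 it does no better than proportion correct, because the short test is the cause.

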## Plan of analysis

### Independent samples t-test

An independent samples t-test will be conducted to compare the average number of hits at the SCT between the control and experimental groups. Age and sex were collected as sociodemographic variables because both have been shown to influence spatial navigation abilities in previous research (
Sneider *et al.*, 2015). Although we did not formulate specific hypotheses regarding the effects of age or sex, these variables were included to confirm group equivalence and to control for potential confounding factors, thereby strengthening the internal validity of our findings. Moreover, to verify that the two groups do not differ significantly in these scores, independent samples t-tests will be conducted to compare the CORSI and SBSOD scores between the experimental and control groups.

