Developing a spatial task that allows users to explore the environment by rotating in a movable chair without the need for forward or backward movement not only leverages several benefits associated with gaze-directed steering (GDS) but also simplifies interaction by eliminating the need for complex movement controls, thus making VR more accessible, especially for users with limited mobility or dexterity.

 A significant advantage expected to feature this setup is represented by the reduced motion sickness. By restricting navigation to rotational exploration should avoid the sensory mismatch that often causes discomfort and enhances situational awareness, allowing users to freely observe their surroundings without the distraction of forward or backward movement.

Moreover, the design controls the visibility of virtual objects, requiring users to piece together information gradually, a feature shared also with the SCT.

This study aims to validate the newly developed VSCT by evaluating participants' performance on the original SCT both before and after VR exposure. We will use a
**between-subjects design**, dividing participants into two groups to clarify the specific effects of spatial versus non-spatial cognitive demands. One group will perform the task in virtual reality, while the other will engage in a non-spatial auditory verbal task, adapted from
Bacon *et al.* (2008), to isolate memory processes from spatial reasoning. To this end, only the first administration of the SCT (T1) will be used for correlation analyses with the VSCT, as it provides a baseline measure of spatial performance. The second administration (T2) is included solely for exploratory purposes—to investigate whether repeated exposure might lead to performance improvements and to preliminarily explore potential training effects. These exploratory findings could inform the design of future studies specifically aimed at assessing the impact of training or interventions. Establishing the VSCT’s validity is a necessary first step before we can confidently use it in such longitudinal or interventional contexts.

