*Procedure*
**

 Participants will be assigned in a pseudo-randomized single-blinded manner to one of the two groups (Auditory Verbal (AV) vs. Virtual Reality (VR)). Both groups will be asked to perform an initial assessment of their spatial abilities using the 40-item version of SCT. In the next phase, the experimental group will be made to wear the "HTC VIVE" visor that will allow them to perform the Virtual Spatial Configuration Task in VR (VR condition); the control group will be administered the auditory verbal memory task (AV condition). Both groups will be given the SCT again at the end of the task (See
Figure 2). 

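### The group comparison of SCT hits is an unadjusted t-test with no stated time point; if it concerns T2, it ignores the T1 score, and no listed analysis uses age or sex

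*Protocol article*

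**What the plan says.** The Procedure section has two arms, VR and auditory-verbal: "Participants will be assigned in a pseudo-randomized single-blinded manner to one of the two groups". Before the condition, "Both groups will be asked to perform an initial assessment of their spatial abilities using the 40-item version of SCT". Afterwards, "Both groups will be given the SCT again at the end of the task". A T1 and a T2 score are therefore planned for everyone.

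The Introduction (Validation of a new 3D spatial task) sets the roles of the two scores. For validity, "only the first administration of the SCT (T1) will be used for correlation analyses with the VSCT". Of the later score it says "The second administration (T2) is included solely for exploratory purposes", namely to look for improvement on repetition and possible training effects that could inform later studies.

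The Plan of analysis (Independent samples t-test) fixes the group comparison: "An independent samples t-test will be conducted to compare the average number of hits at the SCT between the control and experimental groups". On age and sex it says "these variables were included to confirm group equivalence and to control for potential confounding factors". It then adds t-tests on Corsi and SBSOD, "to verify that the two groups do not differ significantly in these scores". The only other analyses listed are a correlation matrix of Corsi, SBSOD, VSCT and SCT, and reliability statistics.

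**The concern.** Three things in one short section do not fit together.

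- The outcome of the main group comparison is not identified, because the SCT is taken twice and the sentence names neither occasion.
- If T2 is meant, a pre-exposure score on the same task is available in both groups and is not used. The estimate is then noisier than it need be, and a chance imbalance in starting ability passes into the T2 difference.
- Age and sex are given the job of controlling confounding, but a two-sample t-test adjusts for nothing, and neither variable appears in any other listed analysis.

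In addition, a non-significant t-test on Corsi or SBSOD is to serve as verification that the groups do not differ, which such a test cannot provide.

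What is at stake is the exploratory training signal, which the article says may inform the design of later studies.

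**Working it through.** **Which administration is tested?** Two readings are possible.

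- *T2.* The Introduction says the study looks at SCT performance before and after VR exposure, with two groups to separate spatial from non-spatial demands. The Corsi and SBSOD checks are introduced as a further, separate step. This favours T2.
- *T1.* The sentences that follow the test concern group comparability, so a baseline check is possible. Adjustment for T1 would then not apply and no precision would be lost. But the test would be only a baseline significance check, and no group comparison of T2 would be planned, although T2 is collected to explore training effects.

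The text needs a change under either reading.

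**Inputs for the T2 reading**

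- From the article: 166 participants and α = 0.05.
- Assumed: a two-sided test; 1:1 allocation; a T1–T2 correlation ρ of 0.3 to 0.7; a true T2 difference of d = 0.3 in units of the unadjusted SD.

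The article gives no sample-size figure for this comparison, so there is none to reproduce. The 166 was calculated for a comparison of two correlations (q = 0.4, power 0.95). By Fisher's z, n per group = 2 × [(1.960 + 1.645)/0.4]² + 3 = 165.4, rounded up to 166. The stated inputs thus give 166 per group, while the text reads as a total. Both group sizes are therefore carried below.

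**Formulas**

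- Residual variance after ANCOVA on T1, relative to the t-test: 1 − ρ².
- Effect in residual SD units: d / √(1 − ρ²).
- Power: two-sample t with noncentrality [d / √(1 − ρ²)] × √(n/2), where n is the group size.

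Example with n = 83 and ρ = 0.5: 1 − 0.25 = 0.75; 0.3/0.866 = 0.346; 0.346 × √41.5 = 2.23; power 60%. Without adjustment: 0.3 × √41.5 = 1.93; power 48%.

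| Analysis | Residual variance | Power at d = 0.3, 83 per group | Power at d = 0.3, 166 per group |
|---|---|---|---|
| t-test | 1.00 | 48% | 78% |
| ANCOVA, ρ = 0.3 | 0.91 | 52% | 82% |
| ANCOVA, ρ = 0.5 | 0.75 | 60% | 88% |
| ANCOVA, ρ = 0.6 | 0.64 | 67% | 93% |
| ANCOVA, ρ = 0.7 | 0.51 | 77% | 97% |

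With 83 per group, the difference detectable at 80% power falls from 0.44 SD to 0.42, 0.38, 0.35 and 0.31 SD for ρ = 0.3, 0.5, 0.6 and 0.7.

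**The balance tests.** An observed standardised difference reaches p < 0.05 only above about 1.97 × √(2/n). That is 1.97 × 0.155 = 0.31 SD with 83 per group, and 1.97 × 0.110 = 0.22 SD with 166 per group. Any smaller imbalance on Corsi or SBSOD would pass as no significant difference.

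**Age and sex.** Set beside the list of analyses (t-tests, correlation matrix, reliability), the stated aim of control has no analysis attached to it.

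**The case against.** The strongest reply is that the article never says the t-test is on T2. A reader might infer that the plan certainly wastes precision, but the documents do not support that: the loss is conditional on T2, and its size depends on a correlation they do not give. This stands, and for that reason the missing time point comes first. At ρ = 0.3 the gain is small (48% to 52% with 83 per group).

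A reader might also infer that the unadjusted comparison is biased. It is not, if the pseudo-randomised allocation works as randomisation: the t-test is then inefficient, and imbalance arises only by chance. Nor is the validation itself at risk. T2 is exploratory, the VSCT–SCT correlation uses T1 only, and nothing is powered on the group difference in SCT.

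Finally, a condensed article may leave a covariate list to a fuller protocol, and this one points to a repository that is not shown. It would go too far to say that age and sex will not be controlled for. But the article does not leave the method open here: it names the test, and that test cannot deliver the control described in the same paragraph. The inconsistency stands as one of the text.

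**Conclusion.** The point holds in a limited form. The article fixes an unadjusted test without naming the administration, and gives age and sex a role that no listed analysis fulfils. Both hold whatever the time point.

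On the T2 reading, the plan also forgoes 9% to 49% of residual variance for ρ between 0.3 and 0.7, with the power gains tabulated above. These figures rest on the assumed ρ, d = 0.3, a two-sided 5% test, 1:1 allocation, and either 166 in total or 166 per group. On the T1 reading there is no precision loss, but the training question has no planned group comparison.

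This is a worthwhile improvement to an exploratory analysis and does not call the main validity analysis into question.

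**What to change.** - State that the group comparison is on T2 SCT hits.
- Analyse it by ANCOVA with group as factor and T1 SCT hits, age and sex as covariates, fixed in advance. Report the adjusted difference with a 95% CI and label it exploratory.
- Describe baseline balance on Corsi and SBSOD by standardised mean differences in place of significance tests, and drop the claim that non-significance verifies that the groups do not differ.
- If age and sex are not to be modelled, remove the statement that they serve to control confounding.

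The cost is a change of analysis wording. All the variables are already collected, and no participant or visit is added.

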**G*Power 3.1**
Faul *et al.* (2009). Assuming a
**moderate to large effect size (Cohen’s q = 0.4)**, a significance level of
**α = 0.05**, and a desired power of
**0.95**, The required sample size for comparing two independent correlation coefficients using a z-test for dependent Pearson’s r was calculated as 166
**participants**. Taken this for granted, and bearing in mind that the data to correlate are not yielded with a paper-and-pencil questionnaire- but a virtual setting requiring training and adaptation, we weight the effect size indication with previous research using similar aims and methods.

This was the case in
da Costa *et al.* (2022), who validated two immersive virtual reality tasks for spatial orientation using correlational and group comparison analyses. The authors reported significant associations between the virtual tasks and traditional cognitive measures, as well as successful group discrimination.

The participants represented a sample size large enough to yield statistically reliable confidence intervals. It should be noted that the study employed a between-subjects design; however, participants from the two groups were combined. In contrast, our study will correlate the two groups with two different variables.

Furthermore,
*
He *et al.* (2022)
* employed a fully within-subjects design to validate a spatial perspective-taking task in ambulatory virtual reality, using a sample size comparable to ours. However, since within-subjects designs typically offer greater statistical power, we acknowledge that our between-subjects design may require a larger sample to achieve equivalent sensitivity. We have accounted for this by adopting a conservative effect size estimate and grounding our decision in the specific demands of VR-based testing, which introduces variability due to training and adaptation phases.

Participants will be actively recruited to participate in the intervention across various University of Bologna Campus locations. Recruitment will be facilitated through targeted advertisements and consecutive enrollment procedures to ensure diverse participant representation and data robustness. 

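### Non-significant t-tests on Corsi and SBSOD cannot verify that the two groups are comparable; report standardised differences with confidence intervals instead (minor)

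*Protocol article*

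**What the plan says.** Three statements in the protocol article's Independent samples t-test section bear on this.

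- SCT hits are compared between groups: "An independent samples t-test will be conducted to compare the average number of hits at the SCT between the control and experimental groups". The section does not say whether this is the first (T1) or second (T2) administration.
- Of age and sex it says "these variables were included to confirm group equivalence and to control for potential confounding factors, thereby strengthening the internal validity of our findings". It names no test or model for them.
- It then adds, joined by a word that continues the same argument, that "to verify that the two groups do not differ significantly in these scores, independent samples t-tests will be conducted to compare the CORSI and SBSOD".

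Under Participants, the sample size rests on comparing the VSCT–SCT correlation with the RAVLT–SCT correlation, and the authors note: "In contrast, our study will correlate the two groups with two different variables". Under Procedure, assignment is pseudo-randomised and each group takes only one of the two tasks, so those correlations come from different people.

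**The concern.** The section asks a significance test to do something it cannot do. A t-test can give evidence that means differ. A failure to reject may reflect alike groups or too little information, and the p-value does not tell these apart.

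The test is unhelpful however the allocation works. If it behaves as randomisation, any significant baseline difference is chance and the test has nothing to discover. If it does not, a real imbalance of modest size can easily pass and be reported as verified comparability.

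At stake is the credibility of statements that compare the two groups: the SCT comparison, and the contrast of correlations used for the sample size. The stated gain in internal validity should not lean on these p-values.

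**Working it through.** **Inputs.** From the article (Participants): α = 0.05, power 0.95, q = 0.4, sample size 166. From the Independent samples t-test section: two verification tests, Corsi and SBSOD. Assumed, because not stated: 1:1 allocation, two-sided tests at 0.05 each, and true imbalances of 0.2 to 0.4 SD.

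**Step 1: the plan's own figure.** For two independent correlations, n per group = 2 × ((z₁₋α/₂ + z₁₋β)/q)² + 3 = 2 × ((1.960 + 1.645)/0.4)² + 3 = 165.4, rounded up to 166. The figure is therefore reproduced as a per-group number (332 in total). The article does not say whether 166 is per group or in total, so both readings are carried: 83 and 166 per group.

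**Step 2: missed imbalance.** The miss probability for one t-test is 1 − power, from the noncentral t distribution with 2n − 2 degrees of freedom and noncentrality d√(n/2). For example, with n = 83 and d = 0.2 the noncentrality is 0.2 × √41.5 = 1.29, the critical value is 1.975, power is 0.249 and the miss probability is 0.751.

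| True difference | Missed, 83 per group | Missed, 166 per group |
|---|---|---|
| 0.2 SD | 75% | 56% |
| 0.3 SD | 52% | 22% |
| 0.4 SD | 27% | 5% |

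**Step 3: what could be observed and still pass.** The largest observed standardised difference that stays non-significant is t₀.₉₇₅ × √(2/n): 1.975 × √(2/83) = 0.31 SD, or 1.967 × √(2/166) = 0.22 SD. These are also the approximate half-widths of the 95% confidence interval for a standardised difference.

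**Step 4: false alarms.** With no true difference and independent scores, the chance of at least one significant result in two tests is 1 − 0.95² = 9.75%. By simulation it is 9.1% if the two scores correlate 0.5.

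**Step 5: spread.** A t-test of means does not examine SDs: simulated with equal means and an SD ratio of 0.7 or 0.8, it rejects about 5% of the time. Correlations do depend on spread. With r = 0.40 and an assumed SCT SD ratio of 0.8, r′ = 0.4 × 0.8/√(1 − 0.16 + 0.16 × 0.64) = 0.33, a shift in q of 0.424 − 0.343 = 0.08. But if the population SDs are equal and scores are normal, a sample SD ratio of 0.8 or less in a given direction has probability P(F ≤ 0.64) = 2.2% at 83 per group and 0.2% at 166. The standard error of q is √(2/(n − 3)) = 0.158 at 83 and 0.111 at 166, so the shift is smaller than the sampling error in either case.

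**The case against.** The strongest reply is that the rule is partly assembled from two sentences. The equivalence wording is attached to age and sex, for which no test is named; for Corsi and SBSOD the text claims only the absence of a significant difference, and no action follows from either result. That is right as to wording. The two sentences nevertheless run on as one argument about comparability, and the declared purpose of the tests is verification, which non-significance cannot supply.

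Several stronger readings are tempting and should not be made.

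- *That the checks often raise false alarms.* Only two verification tests are named. A rate well above 10% needs tests of age and sex that the article never states.
- *That each test is deliberately run without multiplicity control.* The article is silent, and a condensed article may leave this to a fuller plan.
- *That real imbalance is usually missed.* This depends on the reading of 166. On the per-group reading, which reproduces the calculation, 0.3 SD is missed 22% and 0.4 SD 5% of the time; only 0.2 SD is missed more often than not. A true imbalance also presupposes that allocation failed, and nothing in the article shows that it will.
- *That unequal SCT spread will bias the contrast of correlations.* The SD ratio of 0.8 is an assumption that random allocation would rarely produce, and the Fisher-z standard error already covers chance variation in spread.

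It also counts for the authors that they intend to control for confounding, although the article names no model.

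**Conclusion.** The point holds in a limited form. The article offers non-significant t-tests as verification that the groups are alike, and they cannot carry that inference. A true 0.2 SD difference passes more often than not on either reading of the sample size (75% or 56%), while under sound randomisation the tests can only produce meaningless positives, at about 9 to 10%. These figures assume equal allocation, two-sided tests at 0.05 and approximate normality.

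The severity is minor. The VSCT–SCT and VSCT–Corsi correlations, which carry the main validity hypotheses, are computed within the VR group and need no balance between groups. The introduction describes the second SCT as exploratory. Only the SCT group comparison and the VSCT–SCT versus RAVLT–SCT contrast cross the groups.

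**What to change.** - Replace the Corsi and SBSOD verification tests with a table by group of means and SDs (proportions for sex) and standardised differences with 95% confidence intervals, covering T1 SCT, Corsi, SBSOD, age and sex.
- Delete the wording that non-significance verifies comparability or that these variables confirm equivalence.
- Pre-specify that the between-group SCT comparison is adjusted for Corsi, SBSOD, age and sex, and for T1 SCT if the comparison is at T2, whatever imbalance is seen. This gives a concrete form to the article's stated aim of controlling confounding.
- The T1 SCT SD by group, shown in the same table, is useful description because the two contrasted correlations come from different people. No correction of the correlations to a common SD is needed.

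The cost is a few sentences of analysis-plan wording and one table from data already to be collected, with no extra participants. The downside is that the authors give up the simple statement that the groups did not differ significantly, and the intervals will show how much imbalance remains possible: about ±0.31 SD at 83 per group or ±0.22 SD at 166.
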